### Measures

For data collection, each measure will be taken at baseline, 3 months, 6 months, and 1-year postintervention. Evaluation sessions will be recorded, allowing 3 independent evaluators to blindly assess the objective outcome measures. The final assessment (T3) will measure the training retention of participants following therapy sessions.

### Facial Function Assessment Tools: Symmetry and Synkinesis

Different tools will be used to measure the effects of combined therapy compared to fNMR alone on facial symmetry and synkinesis of the participants. First, Emotrics [33], a designed open-source machine learning algorithm, will enable objective facial metrics for patients with facial paralysis. The algorithm uploads a front-view picture of the patient’s face into the program. Then, it automatically places 68 facial landmarks and computes a set of facial metrics relevant to facial palsies, such as palpebral fissure width, smile excursion, and smile and brow symmetry. Second, the FNGS 2.0 [28] and Sunnybrook Facial Grading Scale [19] will be used by 3 independent blinded evaluators to assess facial symmetry at rest, voluntary facial movement, and synkinesis. The FNGS 2.0, also called the modified House-Brackmann scale, is a scale where 4 regions of the face are assessed and scored into different categories depending on the degree of movements and synkinesis presence [34]. It generates a final score between 4 and 24 and converts it into one of the original House-Brackmann categories ranging from I (normal function) to VI (total paralysis). In other words, it incorporates synkinesis scoring and regional scoring to the original validated House-Brackmann scale [28]. As described by Vrabec et al [28], this revised scale presents high inter- and intraobserver agreement with the original scale while providing additional information. On the other hand, the Sunnybrook Facial Grading Scale uses a continuous scale of 0% (total facial paralysis) to 100% (normal facial function and symmetry). This scale has been chosen because of its high sensitivity to changes induced by the intervention [34].

### Patient-Related Outcome Measures: Quality of Life

To measure the effects of combined therapy compared to fNMR alone on the quality of life and psychological issues of the participants, different patient-related outcome measures will be used including the FACE [20] and the Facial Disability Index (FDI) [6]. The FACE assesses 6 main domains: facial comfort, facial movement, oral function, lacrimal control, eye comfort, and social function through 15 questions. Overall, facial function depends on a score previously calculated that ranges from 0 (worst) to 100 (best) [20]. It has been previously demonstrated that FACE effectively discriminates the normal functional state of a person who does not have facial palsy from the state of a person have the disease [20]. Furthermore, the FACE can be used in different clinical contexts, such as assessing the evolution of patients’ facial palsy handicaps from distinct etiologies and reporting changes in patients’ perceptions of social and functional plans [20]. Kahn et al [20] performed an exhaustive process to validate the instrument, which is internationally used for its validity, sensitivity, specificity, and reliability [35]. On the other hand, the FDI has 10 questions that assess 2 domains: physical and social function. Social function scores from 0 (worst) to 100 (best), while physical function scores from −25 (worst) to 100 (best) [6]. Its validity and reliability have been demonstrated by VanSwearingen and Brach [6]. While the FACE scale provides more domains, it lacks measures about specific functional information, such as speech, which is why the use of FDI could be complementary [36].

### Motivation and Adherence to Treatment

To measure the effects of combined therapy compared to fNMR alone on the rehabilitation process of the participants and motivation to treatment, the intrinsic motivation inventory [37] will be used. This multidimensional tool has been developed to assess participants’ intrinsic motivation toward specific activities in laboratory experiments. Interest or enjoyment, perceived competence, effort, pressure or tension, usefulness, perceived choice, and relatedness of a task are all assessed while the participant performs a specific task. The scale has been validated in several contexts [37,38]. Patients’ compliance to treatment will be assessed through intrinsic features of both websites that record metadata every time the participant logs in. These features allow therapists to see if the patient completed their rehabilitation program as recommended. Figure 3 shows an example of the metadata that the MEPP website can generate on an Excel (Microsoft Corp) sheet about compliance with treatment.

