**Methods:**

This study is a randomized controlled trial that compares the effect of fNMR combined with mirror therapy (experimental group: n=45) with fNMR alone (control group: n=45) in 90 patients with peripheral facial palsy presenting with sequelae 3-12 months after onset. Both groups will receive 6 months of rehabilitation training. Facial symmetry and synkinesis; participants’ quality of life; and their psychological factors, motivation, and compliance will be assessed at baseline (T0), 3 months (T1), 6 months (T2), and 12 months (T3) postintervention. Outcome measures are (1) changes in facial symmetry and synkinesis assessed with facial grading tools, (2) quality of life changes with patient questionnaires, and (3) therapy motivation with a standardized scale, as well as adherence to treatment with metadata. Changes in facial symmetry and synkinesis will be judged by 3 assessors blinded to group assignment. Mixed models and Kruskal-Wallis, chi-square, and multilevel analyses will be conducted according to the appropriate variable type.

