### Study Procedures

This trial will compare the effect of mirror therapy in addition to gold standard fNMR (experimental group) over fNMR alone (control group) in patients with peripheral facial palsy dealing with sequelae 3-12 months after onset. During 6 therapy sessions (Textbox 1), all patients will benefit from standardized education on facial anatomy and physiology, eye care, and management of facial dysfunction (eg, eating, drinking, speaking, and nonverbal communication), as well as from rehabilitation to increase symmetry and decrease synkinesis, specific to their needs. These sessions will be provided by speech-language, physical, or occupational therapists, all certified by their respective professional corporation. In addition, a minimum of 5 years of expertise in facial palsy training is required to be included in the study. These clinicians will also perform the different study measurements, but 3 judges (also experts in facial therapy but blinded to therapy allocation) will then analyze the data. The mirror therapy group will also receive modified visual feedback during facial retraining, along with appropriate instructions about its use. In parallel, patients will be prescribed daily specific at-home rehabilitation depending on the nature of their group. Patients in the combined group (mirror therapy plus fNMR) will do their therapy at home with the MEPP 2.0 app [31], while patients in the fNMR group alone will do their therapy at home with the Physitrack app [32]. Figure 2 presents the overall study design.

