**Figure 2 figure2:**
[figure not shown]
Overall study design. Participants in the control group and in the experimental group are assessed at baseline (T0), 3 months postintervention (T1), 6 months postintervention (T2), and 12 months postintervention (T3). fNMR: facial neuromuscular retraining.

Frequency and length of appointment.SessionsSession 1 (1 hour to 1 hour and 30 minutes) for initial assessment and start of management.Session 2 (1 hour) 1 month after session 1.Session 3 (1 hour) 1 month after session 2.Session 4 (1 hour) generally 1-2 months after session 3.Session 5 (1 hour) is generally 3 months after session 4.Session 6 (1 hour) final session generally 6 months after session 5, then discharge to continue independently.The total treatment course will last 12 months.2-3 sessions of 10 to 15 minutes of daily home rehabilitation are expected to be done by the patients from baseline until 12 months.

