### Statistical Analysis

As mentioned, a power calculation was done based on a previous study [23] for the primary outcome (changes from baseline to 6 months). Every measure of facial symmetry and synkinesis will be judged by 3 assessors, blinded to group assignment. Intraclass correlation coefficients will be calculated to ensure interrater reliability, and the resulting means of the assessors’ findings will be used for further statistical analysis. We will first gather descriptive statistics to provide summary data. Then, for continuous variables (Emotrics measurements, Sunnybrook global score, FNGS 2.0 global scores, FACE score, FDI, and intrinsic motivation inventory), a mixed model analysis with patients as random variables and time+group assignment as fixed variables will be considered, with auto-regressive covariance structure, given the structure of the time points for the assessments. Comparison between the timing of recruitment after PFP onset (3-6 months after onset vs 6-9 months vs 9-12 months) and outcomes at T2 and T3 will be specifically measured using multilevel analysis. Kruskal-Wallis analyses will be considered for ordinal variables (synkinesis subscores, symmetry subscores, and motivation subscores). Finally, chi-square analysis will be considered for dichotomous variables (adherence yes or no). Data will be encoded with Excel sheets, and SPSS (IBM Corp) will probably be used for statistical analysis.

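### The motivation inventory is scheduled and modelled at baseline although it rates a performed task, so its T0 score has no treatment task common to both arms behind it and should be left out of the outcome model

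*Protocol article*

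**What the plan says.** - **Schedule.** Methods, Measures: "each measure will be taken at baseline, 3 months, 6 months, and 1-year postintervention". No exception is made for motivation. The Abstract's Methods paragraph names it directly, listing "psychological factors, motivation, and compliance will be assessed at baseline (T0), 3 months (T1), 6 months (T2), and 12 months (T3) postintervention".
- **Instrument.** Methods, Motivation and Adherence to Treatment, states the target as the rehabilitation process and "motivation to treatment, the intrinsic motivation inventory [37] will be used". The same section says that the domains (interest, perceived competence, effort, usefulness and others) "are all assessed while the participant performs a specific task".
- **Model.** Methods, Statistical Analysis, groups the inventory with Emotrics, Sunnybrook, FNGS 2.0, FACE and FDI: "FACE score, FDI, and intrinsic motivation inventory), a mixed model analysis with patients as random variables and time+group assignment as fixed variables". An autoregressive covariance is named. T0 gets no separate treatment.
- **First session.** The appointment textbox after Figure 2 describes session 1 as "for initial assessment and start of management".
- **Arm-specific task.** Methods, Study Procedures: "The mirror therapy group will also receive modified visual feedback during facial retraining". The home apps also differ by arm.

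**The concern.** Sunnybrook, FACE and FDI describe a state that exists before any therapy, so a baseline value is natural for them. On the article's own description, the motivation inventory rates a task. Enjoyment, effort or usefulness of the treatment exercises cannot be rated before they have been tried. Once they have been tried, the two arms are rating different things.

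Greater motivation with mirror therapy is a stated hypothesis and part of the third objective. In a model with time and group but no interaction, one group coefficient is estimated across all visits, T0 included. A T0 score that cannot carry the treatment effect pulls that coefficient toward zero.

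**Working it through.** The article gives no figure for this point, so there is none to reproduce. The check has two parts.

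**1. What can a T0 inventory score refer to?**

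| Timing at T0 | Task rated | Consequence |
|---|---|---|
| Before the first exercises of session 1 | No treatment task yet | Not a rating of motivation toward the treatment |
| After the first exercises of session 1 | With or without modified feedback, by arm | A post-exposure score, not a baseline |
| Before allocation, on a task common to both arms | For example the facial movements of the assessment | Comparable between arms, but not motivation toward the treatment; not stated in the article |

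**2. What does the printed model do with a T0 at which the arms do not differ?**

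Inputs from the article: four visits, 45 per arm, fixed effects for time and group, autoregressive covariance.

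Assumptions:
- The correlation rho between adjacent visits is not given, so 0 to 0.9 is shown.
- The true arm difference is 0 at T0 and a constant 0.6 SD at T1-T3. The article uses 0.6 in its sample-size statement; it is not an estimate for motivation.
- The test is two-sided at .05. The sample-size statement prints .005, which would lower every power below.
- Data are complete, time is categorical, visits count as equally spaced, and the first-order autoregressive matrix is the whole within-patient covariance.

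Formulas for k visits, with unit variance:
- Information I = (k − (k − 2)rho) / (1 + rho)
- Weight of T0 in the group coefficient (k = 4): w0 = 1 / (4 − 2rho)
- Share of the T1-T3 effect estimated: 1 − w0
- Standard error of the group coefficient: sqrt((2/45) / I)
- Power: noncentral t, 90 − 2 = 88 degrees of freedom, noncentrality = effect / standard error

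At rho = 0.5 with T0 included: w0 = 1/(4 − 1) = 0.333, so the share is 0.667 and the expected coefficient is 0.667 × 0.6 = 0.400. I = (4 − 1)/1.5 = 2, so the standard error is sqrt(0.0444/2) = 0.149. Noncentrality is 0.400/0.149 = 2.68, and power is 76%.

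With T1-T3 only: I = (3 − 0.5)/1.5 = 1.667, so the standard error is 0.163. Noncentrality is 0.6/0.163 = 3.67, and power is 95%.

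| rho | w0 | Share estimated | Expected coefficient (SD) | SE with T0 | Power with T0 | SE, T1-T3 only | Power, T1-T3 only |
|---|---|---|---|---|---|---|---|
| 0 | 0.250 | 75% | 0.450 | 0.105 | 99% | 0.122 | nearly 100% |
| 0.5 | 0.333 | 67% | 0.400 | 0.149 | 76% | 0.163 | 95% |
| 0.9 | 0.455 | 55% | 0.327 | 0.196 | 38% | 0.200 | 84% |

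Between these, the share is 71% at rho 0.3 and 62% at rho 0.7. The dilution grows with rho because the autoregressive structure gives the first and last visits more weight.

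**The case against.** **A valid T0 rating could exist.** A reader might infer that no timing can give a usable T0 score. That goes too far: both arms could rate a common task before allocation. The sentence on task performance also follows a general description of the instrument as a laboratory tool, so it need not describe how this trial administers it. This part of the objection stands. But the article names no such task, and a rating of it would not be the motivation toward treatment that the inventory is there to measure.

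**The dilution is not special to motivation.** Randomisation makes the expected arm difference at T0 zero for Sunnybrook, FNGS 2.0, FACE and FDI too, so the additive model dilutes all of them. A time-by-group term would remove the dilution. This is correct: the loss comes from the model. What is particular to motivation is that its T0 score has no treatment task behind it, with or without that term.

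**A post-exposure T0 need not hide the effect in the baseline.** A reader might infer that a T0 taken after the first exercises subtracts part of the effect. That would require a change score or adjustment for T0, and the article states neither for motivation. In the additive model, a T0 carrying a fraction f of the effect leaves a share of 1 − (1 − f)w0. With f = 0.5 as a pure example, that is 0.875 at rho 0 and 0.773 at rho 0.9, so the dilution is milder.

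**The power loss cannot be read from a single-visit test.** A reader might put 0.75 × 0.6 = 0.45 SD into a two-sample t-test with 45 per arm and read off 56%. The factor 0.75 holds only at rho 0, where averaging four visits halves the standard deviation, and power there is 99%.

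**The wording is tentative and the outcome is not primary.** The model is one that will be considered, and motivation is not identified as the primary outcome. This limits the weight of the point. The model is still the only analysis given for the inventory's overall score, and the schedule is stated without reservation.

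**Conclusion.** The point holds as a moderate one. Schedule, instrument and model are all printed, and taken together they feed into the group effect a T0 score that has no treatment task behind it or follows an arm-specific one.

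If the model is fitted as printed and the arms do not differ at T0, the group coefficient is 75% (rho 0) to 55% (rho 0.9) of the T1-T3 effect. Power with T0 included against T1-T3 only is 99% against nearly 100% at rho 0, 76% against 95% at rho 0.5, and 38% against 84% at rho 0.9. The practical loss is therefore negligible at low correlation and large at high correlation. Both rho and the 0.6 SD effect on motivation are assumptions, so these figures show a range and do not predict this trial's power.

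**What to change.** 1. Leave T0 out of the outcome vector for the inventory. Compare the arms on its T1-T3 scores as post-exposure values, and add the matching exception to the Measures section and the Abstract.
2. If a T0 score is kept, define it as a rating, before allocation, of a named task common to both arms, and use it only as a covariate.
3. Remove compliance from the T0 schedule in the Abstract. Login records cannot exist before the apps are in use. The planned chi-square analysis of adherence needs no change.

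The cost is a few sentences, with one questionnaire fewer at baseline under step 1. The downside is that there will be no within-patient change score for motivation.

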**Figure 3 figure3:**
[figure not shown]
Example of metadata about compliance with the Mirror Effect Plus Protocol website.

### Statistical Analysis

As mentioned, a power calculation was done based on a previous study [23] for the primary outcome (changes from baseline to 6 months). Every measure of facial symmetry and synkinesis will be judged by 3 assessors, blinded to group assignment. Intraclass correlation coefficients will be calculated to ensure interrater reliability, and the resulting means of the assessors’ findings will be used for further statistical analysis. We will first gather descriptive statistics to provide summary data. Then, for continuous variables (Emotrics measurements, Sunnybrook global score, FNGS 2.0 global scores, FACE score, FDI, and intrinsic motivation inventory), a mixed model analysis with patients as random variables and time+group assignment as fixed variables will be considered, with auto-regressive covariance structure, given the structure of the time points for the assessments. Comparison between the timing of recruitment after PFP onset (3-6 months after onset vs 6-9 months vs 9-12 months) and outcomes at T2 and T3 will be specifically measured using multilevel analysis. Kruskal-Wallis analyses will be considered for ordinal variables (synkinesis subscores, symmetry subscores, and motivation subscores). Finally, chi-square analysis will be considered for dichotomous variables (adherence yes or no). Data will be encoded with Excel sheets, and SPSS (IBM Corp) will probably be used for statistical analysis.

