## Methods

### Eligibility Criteria

To be included in the study, patients must be 18 years or older, experiencing their first PFP, be from 3 months to 12 months after onset, and must have a score 4 or 5 on Facial Nerve Grading System 2.0 (FNGS 2.0) [28]. In addition, they must have sufficient cognitive status, measured by a cutoff score of 23 on the Montreal Cognitive Assessment [29,30], and present with no active mental health diagnosis. They should also not present with a history of neurologic diseases affecting facial function. Patients with concomitant therapies or botulinum toxin type A injections, presenting with bilateral palsies or with medically uncontrolled metabolic diseases, will be excluded from the study. Access to an internet connection and basic computer literacy will also be verified as eligibility criteria.

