### Recruitment and Compensation

As determined, thanks to a power calculation measure based on Martineau et al [22] to reach a power of 0.8 with a size effect of 0.6 and an α of .005, 90 patients with peripheral facial palsy of diverse etiologies in the paretic (n=30), early synkinetic (n=30), or chronic synkinetic phase (n=30) will be recruited to the study. They will then be randomized into 2 groups, mirror therapy plus fNMR or fNMR alone, by computerized block randomization. No compensation or incentive is planned to be provided at this time. Recruitment is planned to be conducted in 3 tertiary care centers (hospitals) in Canada, England, and Belgium (Hôpital Maisonneuve-Rosemont, Queen Victoria Hospital, and Sint-Augustinus GZA Hospital, respectively). A telehealth option will be available for the participants via institutionally secured platforms.

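### The only model stated for the continuous outcomes does not use the T0 score as a covariate, so a 6-month change comparison would be valid but less precise than it could be at almost no cost

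*Protocol article*

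**What the plan says.** The Measures section states that "each measure will be taken at baseline, 3 months, 6 months, and 1-year postintervention". The Statistical Analysis section says that the power calculation was done "for the primary outcome (changes from baseline to 6 months"; that sentence does not name the scale. For Emotrics, Sunnybrook, FNGS 2.0, FACE, FDI and the motivation inventory the same section proposes "a mixed model analysis with patients as random variables and time+group assignment as fixed variables will be considered", with an autoregressive covariance. It mentions no baseline covariate and no constraint that the arms share one T0 mean.

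Recruitment and Compensation gives the sample size basis: "to reach a power of 0.8 with a size effect of 0.6 and an α of .005, 90 patients with peripheral facial palsy". The arms have 45 patients each.

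**The concern.** The baseline score of each continuous facial and quality-of-life measure is already in hand, and it usually predicts the 6-month score. The stated list of fixed effects does not use it as a covariate. Baseline then enters in one of two ways.

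- **As a subtraction.** This is the change score, or a group-by-time contrast with T0 as an ordinary response and a separate T0 mean in each arm. With complete data the two give the same estimate. It fixes the slope on baseline at 1, whatever the data say, and so over-corrects a chance baseline difference.
- **As one more visit in the printed time+group model.** The group coefficient then averages over visits including T0, and carries part of any chance T0 difference forward.

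What is at stake is precision. The target is 80% power and the article mentions no allowance for dropout, so precision available from data already collected is worth having.

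**Working it through.** **Inputs from the article:** 45 per arm; effect size 0.6; power 0.8; alpha printed as .005. **Not given:** rho, sidedness, and whether 0.6 is scaled by the SD of the score or of the change. I take two-sided tests, no dropout, equal variances at T0 and T2, and rho from 0.3 to 0.8.

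**1. The plan's own figure.** For a two-sample t test with d = 0.6 and 80% power, two-sided alpha .05 needs 90 patients in total, which matches the plan. Two-sided alpha .005 needs 152. With 45 per arm, power is 0.804 at .05 and 0.490 at .005. The printed alpha therefore does not yield 90. Both values are carried below.

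**2. Variances, in units of the score variance.**
- Change score: 2(1 − rho)
- Baseline-adjusted: 1 − rho²
- Ratio: (1 − rho²) / [2(1 − rho)] = (1 + rho)/2

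At rho 0.5 the ratio is 0.75, a 25% cut. That is worth 1/0.75 = 1.33 times the patients. The ratio is below 1 for every rho below 1.

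**3. Power at two-sided alpha .05** (noncentral t; 88 df unadjusted, 87 df adjusted).

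On the change SD, d is 0.6 unadjusted and 0.6/√((1+rho)/2) adjusted. On the score SD, d is 0.6/√(2(1−rho)) unadjusted and 0.6/√(1−rho²) adjusted.

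| rho | 0.6 on change SD | 0.6 on score SD |
|---|---|---|
| 0.3 | 0.804 to 0.937 | 0.662 to 0.839 |
| 0.5 | 0.804 to 0.901 | 0.804 to 0.901 |
| 0.7 | 0.804 to 0.863 | 0.953 to 0.976 |
| 0.8 | 0.804 to 0.843 | 0.994 to 0.997 |

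The gains are about 13, 10, 6 and 4 points on the first reading, and about 18, 10, 2 and 0.3 points on the second. At rho 0.5 the two readings coincide, because 2(1 − 0.5) = 1.

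**4. At the printed alpha .005, rho 0.5:** 0.490 to 0.657, about 17 points.

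**5. Chance imbalance at T0.** With 45 per arm, the T0 difference in means has SD √(2/45) = 0.211 score SDs.
- *Change score.* Given a T0 difference D, the estimate shifts by −(1 − rho)D, which is −0.5D at rho 0.5.
- *Printed time+group model with T0 in the response.* Take AR(1) over four visits with T0–T2 correlation 0.5, so the adjacent-visit correlation is r = √0.5 = 0.707. Ignore the random patient effect. The visit weights are proportional to 1, 1 − r, 1 − r, 1, which gives 0.387, 0.113, 0.113, 0.387. Carry-over is 0.387 + 0.113(0.707) + 0.113(0.5) + 0.387(0.354) = 0.66. A one-SD imbalance then moves the group coefficient by 0.66 × 0.211 = 0.14 score SDs.

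The two routes err in opposite directions, so they should not be merged into one figure.

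**The case against.** **This belongs in the SAP.** The paragraph is provisional, and covariates are often left to a fuller document. That is fair as to tone. Yet the article does more than stay silent: it lists the fixed effects, offers no other model for these outcomes, and leaves the T0 score out.

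**The power loss is not a loss from the printed model.** This stands. A reader might infer that the trial as written forfeits about 10 points. That figure compares a change-score contrast with an adjusted one, at rho 0.5 and alpha .05. The printed model has no group-by-time term, so its group effect is not the 6-month change at all. That is a separate and probably larger matter. Adding the term with T0 left free still leaves the change-score inefficiency.

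**The result is biased.** A reader might infer this from the imbalance figures. It does not follow for the change-score comparison. Under randomisation that comparison is unbiased, and chance imbalance is already part of its standard error.

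**Restricted entry makes it worse.** Patients "must have a score 4 or 5 on Facial Nerve Grading System 2.0", and a reader might infer that the narrowed range lowers rho and so raises the gain. The article gives no correlation for any scale, so this cannot be shown.

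**Every outcome and the primary model are affected.** Neither label is supported. Adherence comes from log-in metadata and has no natural T0 score. The article never calls the mixed model primary; it is simply the only one stated for the continuous outcomes.

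**Conclusion.** The point holds as a question of efficiency, for continuous outcomes with a pre-treatment T0 score (Sunnybrook, FNGS 2.0, Emotrics, FACE, FDI). A 6-month comparison based on change from baseline is valid but less precise than a baseline-adjusted one whenever rho is below 1.

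The size cannot be fixed from the article. At two-sided alpha .05 the gain runs from about 18 points (rho 0.3, 0.6 on the score SD) to under 1 point (rho 0.8, same scaling), and is about 10 points at rho 0.5 on either scaling. At the printed .005 and rho 0.5 it is about 17 points. These figures assume complete data and equal variances. No single number should be quoted until alpha, the scaling of the 0.6 and a plausible rho are settled. The change is worth making because the direction is certain and the cost is close to nothing.

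**What to change.** In Statistical Analysis, take the T1 to T3 scores as the response. Use as fixed effects the T0 score of the same measure, T0-by-time, group, time and group-by-time. Name the adjusted group difference at 6 months (T2) as the primary estimate. Apply the same form to every continuous outcome with a pre-treatment T0 score.

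A close alternative keeps T0 in the response, includes group-by-time, and constrains both arms to one T0 mean. The two are not identical under an autoregressive covariance, because the covariance structure then sets the implied slope on baseline.

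The cost is a sentence of text, up to three degrees of freedom (T0 and T0-by-time over three visits), and a simple rule for a missing T0 value under the covariate form. It needs no new data, visits or patients, and should be fixed before any unblinded data are seen. The printed alpha should be reconciled with the 90 patients at the same time, and the SD behind the 0.6 stated.
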